#### Cost

A major issue in evaluating the effectiveness of any early intervention model is to understand the cost of the intervention. Detailed cost measures regarding each component of the study, including intervention, assessment, and operational costs, were collected to document costs, and estimate cost benefit and/or cost effectiveness analyses.

#### Data sources

Detailed records of expenditures were kept for each resource category of labor, materials, equipment, buildings and facilities, and miscellaneous, as well as records of donated items. These records were supplemented by staff cost and activities diaries; *Legacy* staff members who routinely perform three or more *Legacy* activities were required to complete time and activity diaries. Each diary detailed specific activities and the respective amounts of time spent on each *Legacy* activity. These diaries were collected semi-annually.

### Analytic plan

#### Statistical approach

As described in the measurement section, *Legacy* gathered a rich dataset that included quantitative assessments of mothers and their children, qualitative ethnographic and quantitative process data from the intervention sessions, and cost data related to the administration and evaluation of the intervention as a whole. Throughout the course of the intervention, these data were described and compared across groups by intervention site through the use of classic intent-to-treat (ITT) analytic methods. The general analytic plan is described below.

#### Descriptive statistics

Descriptive statistics will be used with *Legacy* data for at least three purposes: 1) to compare the mothers who consented to participate in *Legacy* to the entire screened sample; 2) to examine the initial comparability of the intervention and comparison groups, 3) to provide a rich description of the Legacy mothers and their children at each time point. For group comparisons, parametric statistics will be used where appropriate and non-parametric statistics will be used where the assumptions needed for parametric tests are not met. For continuous variables, *t*-tests will be used to examine group differences and for categorical data Chi-square statistics will be calculated. For preliminary descriptive group comparisons, simulations, the Bonferroni correction method, or a false discovery rate approach will be used to account for multiple comparisons within an assessment domain.

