#### Modification of main study inclusion criteria as a function of pilot findings

Several important lessons were learned from the pilot study recruitment process. First, the formal screening procedures used to identify maternal mental health and substance use problems were difficult and unreliable to implement in the pilot, so formal screening for these issues was dropped. However, clinic and hospital staff assisted *Legacy* staff by referring only mothers with no known medical risk factors, such as maternal mental health problems, substance use problems, and high-risk pregnancies. Second, the pilot study recruitment proceeded very slowly, particularly in Miami. The majority of mothers approached at that site could not be included because they were ineligible, rather than not being interested. Specifically, 249 of 316 mothers (79%) approached in Miami for the pilot were ineligible. Only 7 eligible mothers (10%) choose not to participate. In comparison, of 106 LA mothers screened for the pilot, 31 (29%) were ineligible, and 12 eligible mothers (16%) chose not to participate. The low eligibility rate of the Miami mothers, if it continued into the main study, would limit the generalizability of the results. Preliminary analyses also revealed that the mothers included in the Miami pilot were significantly less resourced and were at greater demographic risk than the LA mothers (61% vs. 40% household income < $20,000; 13% vs. 22% married, 71% vs. 43% living in neighborhoods with high unemployment), probably due to differences in how poverty was operationalized at the sites. Therefore, inclusion criteria were broadened and aligned across the two sites for the main study.

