### Recruitment and randomization

After the main study inclusion criteria were established and sample size calculations were complete, recruitment began. Mothers were recruited at prenatal WIC clinics in LA and at birth hospitals in Miami. Due to differences in the point of recruitment, the enrollment process varied slightly between sites.

In LA, the recruitment process began at a set of prenatal clinics within the catchment zip codes. Mothers were either approached by clinic staff or by recruiters directly. Interested mothers were told about the study using a scripted format and an eligibility screener was conducted. Interested mothers completed the screener and then, if eligible, the consent process was initiated at the clinic. The recruiters also secured consent at a later date if interested mothers felt that they could not immediately grant consent for their participation. In Miami, the recruitment process began at the well-baby unit of the recruitment hospitals soon after the mothers delivered their babies. Recruitment was conducted using a two-step process. The recruiters first approached mothers in the well-baby unit, with information about the study delivered using a scripted format. An eligibility screener was completed by all interested mothers. Within two weeks, eligible mothers received a follow-up visit by the recruiter at the homes of the mothers to complete informed consent and enrollment in the study.

Blinded randomization of the consenting participants was performed within each site (neither the site staff nor the participants knew the group assignment at enrollment) via a centralized, computer-generated process at the PCC. Assignments to either the intervention or comparison group were made on a weekly basis for enrolled participants. After randomization, the intervention site teams received assignments from the PCC and communicated them to the mothers.

To protect the rights of the research participants, mothers were asked for consent not only at the initial enrollment but again annually before each assessment visit. Separate consents were received for additional qualitative data collection on subgroups, including focus groups and case study interviews. Human subjects reviews were conducted by the Institutional Review Boards at CDC, at RTI, at UCLA, at UM, and at Western IRB for the time between 2005 and 2008 when UM contracted with them to conduct human subjects protection reviews.

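### Consenting mothers are to be compared with a screened sample that contains them, so the planned two-sample tests are too conservative, by an amount that depends on the consent share

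*Protocol article*

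**What the plan says.** The Descriptive statistics section of the analytic plan gives three purposes. The first is "to compare the mothers who consented to participate in *Legacy* to the entire screened sample". The second is baseline comparability of the randomised groups, and the third is description of the sample at each time point. The section then gives one general rule for group comparisons: for continuous variables t-"tests will be used to examine group differences and for categorical data Chi-square statistics will be calculated". The fallback is that "non-parametric statistics will be used where the assumptions needed for parametric tests are not met". The section names no method for overlapping groups and no comparison of consenters with non-consenters.

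Recruitment and randomization gives the order of events. In LA, "Interested mothers completed the screener and then, if eligible, the consent process was initiated at the clinic". In Miami, "An eligibility screener was completed by all interested mothers", and consent followed at a home visit within two weeks.

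The section on changes to the inclusion criteria after the pilot reports that "249 of 316 mothers (79%) approached in Miami for the pilot were ineligible" and that "Only 7 eligible mothers (10%) choose not to participate". For LA it reports 106 screened, 31 ineligible and 12 eligible mothers who declined.

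**The concern.** Because consent follows the screener, the consenters are a subset of the screened sample. The t-test and the chi-square test both take their reference distribution from two independent groups. When one group is nested in the other, the shared mothers pull the two means together and the usual standard error no longer describes the difference. Two-sample rank tests need independent groups too, so the non-parametric fallback does not help.

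This comparison is the plan's stated check on how enrolled mothers relate to those screened, and the article treats generalisability as a concern both in the pilot findings and under Study limitations. If the consent share is high, a non-significant result would look reassuring when the test had little chance of showing a modest difference.

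The screened sample also includes ineligible mothers. A difference from it therefore combines the effect of the criteria with the effect of willingness to consent, and cannot be assigned to either.

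**Working it through.** **Inputs.** The article gives no figure for this comparison, so there is none to reproduce. Its pilot percentages do check: 249/316 = 79%, 7/67 = 10%, 31/106 = 29%, 12/75 = 16%.

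- Miami pilot: 316 - 249 = 67 eligible; 67 - 7 = 60 consented; f = 60/316 = 0.19 (treating those approached as screened).
- LA pilot: 106 - 31 - 12 = 63 consented; f = 63/106 = 0.59. The 63 comes from subtraction; the article describes the pilot as 60 dyads per site.
- Main-study consenters: 300 in Miami and 315 in LA (Sample size and power).
- Main-study numbers screened: not in the text shown, so f is assumed. I use the two pilot shares and 0.40 between them.
- Significance level for this comparison: not stated; two-sided 0.05 assumed.

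**Formulas.** Let n mothers consent out of N screened, f = n/N, with common standard deviation s.

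- Contrast: mean(consenters) - mean(all screened) = (1-f) × [mean(consenters) - mean(non-consenters)].
- True variance of that contrast: s²(1/n - 1/N) = s²(1-f)/n.
- Variance the two-sample test assumes: s²(1/n + 1/N) = s²(1+f)/n.
- Standard error too large by sqrt((1+f)/(1-f)).
- Actual two-sided size: 2[1 - Φ(1.96 × sqrt((1+f)/(1-f)))].

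**Size.**

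| f | n of N | SE inflation | Effective critical value | Actual size |
|---|---|---|---|---|
| 0.19 | 300 of 1,580 | 1.21 | 2.38 | 0.018 |
| 0.40 | 300 of 750 | 1.53 | 2.99 | 0.003 |
| 0.59 | 315 of 530 | 1.98 | 3.89 | 0.0001 |

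Simulation at the pilot sample sizes (20,000 replicates) agrees. Miami's share gives 0.017 for the t-test and 0.020 for chi-square; LA's gives 0.00005 for both.

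**Power** (normal approximation), stated test against consenters versus all screened non-consenters:

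| f | 0.25 SD, stated | 0.25 SD, disjoint | 0.50 SD, stated |
|---|---|---|---|
| 0.19 | 0.94 | 0.97 | 1.00 |
| 0.40 | 0.64 | 0.92 | 1.00 |
| 0.59 | 0.14 | 0.81 | 0.96 |

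Worked case at f = 0.59: a true 0.25 SD difference appears as 0.41 × 0.25 = 0.10 SD. The test needs 1.96 × sqrt(1.594/315) = 0.139 SD to reject. The true standard error is sqrt(0.406/315) = 0.036, so power is 1 - Φ((0.139 - 0.101)/0.036) = 0.14.

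**Make-up of the non-consenters.** In the Miami pilot 249 of 256 were ineligible and 7 were eligible decliners. In LA 31 of 43 were ineligible and 12 were decliners. The disjoint column above therefore still mixes eligibility with consent.

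**Consented versus eligible-declined.** Scaling the pilot fractions to the main study gives 315 × 12/63 = 60 decliners in LA and 300 × 7/60 = 35 in Miami. Power at 0.30 SD is about 0.57 (315 vs 60) and 0.39 (300 vs 35).

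**The case against.** The strongest reply is that the sentence naming the tests is general and does not mention the first purpose. A side-by-side description of enrolled and screened mothers would fit the text, and in a condensed article the coding of consent status could be left to the analysis plan. That lowers the weight of the point. But the rule covers group comparisons and follows a list whose first item is one, so on a plain reading the tests apply to it.

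A second reply is that comparing enrolled mothers with everyone screened, ineligible mothers included, speaks directly to the article's worry about Miami's low eligibility rate. That is fair. The purpose is legitimate, and separating the groups serves it better than dropping the ineligible mothers.

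Three stronger readings are tempting and not supported:

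- That the test addresses the wrong null hypothesis. Consenters equal all screened exactly when they equal the non-consenters (f < 1). Only the reference distribution is wrong.
- That the comparison can rarely detect selection. At f = 0.19 power is 0.94 at 0.25 SD, and at f = 0.59 it is 0.96 at 0.50 SD. The loss is severe only for a high consent share combined with a modest difference.
- That Miami's 79% ineligibility carries into the main study, so that eligibility would dominate the result there. The criteria were broadened because of that figure, and nothing in the article says how far ineligible mothers differ from the rest. A higher eligibility rate would raise f and make the overlap worse, but the main-study share is unknown.

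**Conclusion.** The point holds as a minor one. As written, the comparison uses nested groups with tests for independent groups, and the result is conservative: slightly at a consent share near 0.19, substantially near 0.40, and severely near 0.59 for differences of about 0.25 SD. A non-significant result at a high consent share should not be read as evidence that consent was unselective, and a significant one cannot be attributed to consent alone.

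The sizes rest on an assumed f, a two-sided 5% level, a common standard deviation, and the reading that the general test sentence covers this purpose. The direction of the error depends on none of the numerical assumptions. Randomisation, the outcome analyses and the sample size are unaffected.

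**What to change.** Reword the first descriptive purpose so that, within each site, consenting mothers are compared with screened mothers who did not consent. Show the latter as two groups, eligible but declined and ineligible. Read consented versus eligible-declined for consent selection, and eligible versus ineligible for the effect of the criteria. Report each difference with a 95% confidence interval.

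The cost is about one sentence in the plan, and the screener data were already collected. The downside is precision: few eligible mothers declined in the pilots (10% in Miami, 16% in LA), so the consent contrast will have wide intervals. At 35 to 60 decliners the half-width is about 0.35 SD in Miami (1.96 × sqrt(1/300 + 1/35)) and 0.28 SD in LA (1.96 × sqrt(1/315 + 1/60)). An interval shows that limit openly, which a non-significant test against the whole screened sample would not.

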#### Analyses of outcome and mediating factors

In general, all intervention effects will be investigated using site- and time-point-stratified models first, using an ITT approach. Due to important implementation differences, site pooled models with site interaction included, will be considered carefully and used sparingly. The primary outcomes will be first examined using *t*-test and Chi-Square analyses to investigate individual outcomes as a function of *Legacy* group assignment. Multivariate statistical modeling will be used to address changes over time as well as the effects of mediating and moderating variables. Given the longitudinal nature of the data, trend analyses will be employed to test for linear and curvilinear relationships in the repeated measures over time. In the anticipated event that significant group differences are detected in maternal and child mediators and outcomes, multivariate linear and logistic regression techniques will be employed as a means of identifying effect modification and controlling for significant confounders. All regression modeling procedures will follow the general conceptual path of influence described in the *Legacy* Logic Model (Figure 2). Multiple ANOVA or regression models that account for correlation of outcomes within subjects will be employed to model the collective influence of intervention randomization on multiple measures of a single outcome domain (e.g., cognitive/language outcomes). In anticipation of an increasing amount of missing data over time, multiple imputation and nonresponse weighting will be used as alternative means of conducting ITT analyses within a general PROC MIXED regression framework.

A strength of the *Legacy* evaluation is a design in which many mediators and outcome variables are measured at multiple time points. This will allow a mixed model approach. In the first stage, growth curves are fit for individuals. Depending on the number of measurement, these curves may be linear, quadratic, etc. In the second stage, predictors such as intervention or comparison group assignment, demographic characteristics, and other predictors will be added and evaluated for their ability to predict slope and intercept parameters.

Further, structural equation modeling will be used, as appropriate, to estimate multiple and interrelated dependence relationships and to represent unobserved concepts in these relationships and account for the measurement error in the estimation process. This type of analysis will be used to fit measurement and structural models based on the *Legacy* Logic Model. Models will incorporate multiple paths and mediating relations; in short, the models will represent paths through which the *Legacy* intervention might have an effect. In addition, multi-group models will allow us to compare sites, demographic groups, and the randomization groups for equivalency. A variety of indices will be used to evaluate these models.

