We chose an effect size of 0.50 for the age-appropriate cognitive measure in this study. Several considerations led to this choice. First, *Legacy* might be considered less intensive, with reference to the group leader working directly with the child, than some previous early intervention studies. A second consideration is that although previous parenting interventions found small effect sizes, this intervention will be different in intensity than these programs. The intervention will most likely be more intensive with reference to parent–child interaction than previous parenting interventions. A third consideration was the unknown level of noncompliance that would be encounter in the intervention group. In the Infant Health and Development Program, the level of program participation was found to be strongly related to the estimated effect size, with the observed difference in mean Stanford-Binet scores between the intervention subgroup with the lowest participation rate and the comparison group being about .25 standard deviations [62]. The level of intensity, with reference to previous early intervention and parenting programs, and low participation in the intervention by intervention families have the potential to affect the observed effect size.

Another important element to take into consideration when calculating sample size is the participant loss rate. The literature indicated a wide range, 7% to 70%, of subject loss rates for various early intervention programs [56,63]. The 7% loss rate was for a highly structured study where extraordinary measures were taken to minimize subject drop out [63]. It was highly unlikely that similar measures could be be employed in this study. Most studies have shown a 30% to 40% loss rate (37% [64]). Even with a conservative, anticipated loss rate of 50% by age five, the study would still have a power of 0.86 for detecting an effect size of 0.50 at each site. It should be noted that this sample size (120) refers to the total number of children (intervention and comparison) for whom data on an age-appropriate cognitive measure will be available at the end of the assessment period (age five). The computations assume a one-sided test at the alpha = 0.05 level. A one-sided test was chosen since the available literature on early intervention gives no indication of a detrimental effect on a child’s development.

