Based on data from the pilot study, we had a 50 - 70% attendance in the mothers’ groups. In order to ensure a practical group size (approximately 7–10 per group) we decided to recruit 15 intervention mothers per group for the main study, resulting in a recruitment ratio of 15 intervention mothers to 10 comparison mothers. Because we experienced approximately an 80% assessment compliance rate, we did not increase the number of comparison mothers. The pilot study also suggested that the rate of fetal loss that should be expected among the prenatally recruited LA participant group was 5%. Therefore, the final main study sample included 300 Miami and 315 LA participants who were randomized in a ratio of 3 intervention: 2 comparison, resulting in 180 intervention and 120 comparison participants in Miami, and 190 intervention and 125 comparison participants in LA. Post-randomization, 9 participants became ineligible due to fetal loss (*n* = 3) and administrative recruiting errors (*n* = 6).

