Other	5.8%	3.9%	7.9%	0.0446
English Spoken Most in Home	79.8%	85.1%	74.4%	0.0014
Home Ownership				
Owned	22.5%	29.2%	15.7%	<.0001
Rented	75.9%	69.8%	82.2%	
Occupied without rent payment	1.6%	1.0%	2.1%	
Lives in public housing	12.6%	14.5%	10.7%	0.1778
Household Composition		Mean		p-value
Number of adults living in home^	1.5	1.6	1.5	0.5781
Number of children living in home+	1.5	1.5	1.4	0.7054

* As indicated by Chi-square or *t*-test statistic, as appropriate.

^Excluding *Legacy* mother, top-coded at 6.

+ Excluding *Legacy* child.

Statistical comparisons of intervention and comparison groups were conducted within sites to identify any group differences that may have remained after group randomization. As depicted in Table 2, randomization of eligible participants to each of the two randomization groups within each site resulted in equivalence of groups across each measured sociodemographic characteristic.

**Table 2 T2:** Baseline socio-demographics for mothers in the Miami and LA samples and the combined sample, by randomization group

	**Miami (n=289)**		**LA (n=285)**	
	**%**		**%**	
	**Interv.**	**Comp.**	**Interv.**	**Comp.**
Maternal Age < 23	55.5%	59.5%	40.6%	42.5%
Child Gender				
Male	47.4%	49.1%	56.5%	46.1%
Female	52.6%	50.9%	43.5%	53.9%
Education				
Less than HS diploma	29.5%	25.0%	21.8%	17.5%
HS diploma or more	70.5%	75.0%	78.2%	82.5%
Marital Status				
Married	14.5%	16.4%	26.7%	27.5%
Not Currently Married	85.6%	83.6%	73.3%	72.5%
Live with a Husband/Partner	33.7%	31.0%	47.8%	45.3%
Race/Ethnicity (multiple selections allowed)				
Non-Hispanic Black	65.9%	74.1%	43.6%	46.7%
Non-Hispanic White	1.7%	0.0%	5.5%	8.3%
Hispanic	9.8%	7.7%	43.6%	37.5%
Haitian	18.5%	14.7%	1.2%	3.3%
Other	4.1%	3.5%	6.4%	4.6%
Employment				
Working full- or part-time	21.4%	21.6%	28.5%	32.5%
Not working	78.6%	78.5%	71.5%	67.5%
Household Income				
<$20,000	53.8%	50.9%	49.7%	45.0%
>= $20,000	38.7%	37.1%	42.2%	48.3%
Missing	7.5%	12.1%	7.9%	6.7%
Languages Spoken at Home				
Non-English language	34.7%	34.5%	50.9%	49.2%
	Mean		Mean	
Household Composition				
Number of adults living in home*	2.6	2.6	2.5	2.5
Number of children living in home^	1.4	1.5	1.4	1.5

* Excluding *Legacy* mother, top-coded at 6

^ Excluding *Legacy* child

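### The multivariable regression step is conditional on a significant unadjusted difference and adjusts for significant confounders; it should use a fixed covariate set for every primary outcome

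*Protocol article*

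**What the plan says.** The Protocol article, under 'Analyses of outcome and mediating factors', sets an order. Primary outcomes are examined first by group with t-tests and chi-square tests, by site and time point, under intention to treat. Regression then follows "In the anticipated event that significant group differences are detected in maternal and child mediators and outcomes", and its stated purpose is to identify "effect modification and controlling for significant confounders".

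The same section plans other models without this condition:
- trend analyses;
- models for several measures of one domain;
- multiple imputation and nonresponse weighting in a mixed-model framework;
- growth curves whose second stage adds group assignment and demographic characteristics, each judged by how well it predicts slope and intercept.

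'Sample size and power' bases the design on a cognitive measure: "the study would still have a power of 0.86 for detecting an effect size of 0.50 at each site", where "this sample size (120) refers to the total number of children (intervention and comparison" with data at age five. It adds: "The computations assume a one-sided test at the alpha = 0.05 level".

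'Participant characteristics' reports that randomisation "resulted in equivalence of groups across each measured sociodemographic characteristic".

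**The concern.** In a randomised comparison, adjustment for prognostic baseline factors mainly serves precision. It does that job only if the covariates are fixed in advance and the model is fitted whatever the unadjusted test shows. The written rule works the other way. An outcome that narrowly misses significance does not receive this more precise regression. An outcome that passes is re-estimated because it passed, so its adjusted estimate inherits the selection. Choosing covariates by significance adds a second dependence on the data. Power for effects smaller than the design value is at stake, and so is the credibility of the adjusted estimates that reach print.

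**Working it through.** **Inputs from the article.** One-sided alpha 0.05, effect size 0.50, 120 analysable children per site after an "anticipated loss rate of 50% by age five", and participants "randomized in a ratio of 3 intervention: 2 comparison" ('Sample size and power'). Year 5 assessments: Miami 122 and 73, LA 117 and 73 (Table 4). Effects below 0.25 are cited for earlier parenting programmes and serve here as a sensitivity value.

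**Assumptions.** The article gives no share of outcome variance explained by covariates (R²); 0.10 to 0.30 is assumed. The first-step test is taken to be the one-sided 0.05 test of the sample size section.

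**1. The plan's own figure.** With 60 per group, SE = √(1/60 + 1/60) = 0.1826 SD. Then 0.50/0.1826 − 1.645 = 1.094, which gives power 0.863 (noncentral t 0.860). With 3:2 allocation (72 and 48) it is 0.850. A two-sided test gives 0.78 or 0.77. The stated 0.86 is therefore reproduced, and it rests on an unadjusted one-sided comparison.

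**2. Precision given up, Miami Year 5.** SE = √(1/122 + 1/73) = 0.148. Adjustment multiplies it by √(1 − R²). The effect detectable with 80% power is (1.645 + 0.842) × 0.148 × √(1 − R²). Power is from the noncentral t.

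| R² | Detectable effect (SD) | Power at 0.50 | Power at 0.25 | Equivalent sample, 1/(1 − R²) |
|---|---|---|---|---|
| 0 | 0.37 | 0.96 | 0.52 | 1.00 |
| 0.10 | 0.35 | 0.97 | 0.55 | 1.11 |
| 0.20 | 0.33 | 0.98 | 0.59 | 1.25 |
| 0.30 | 0.31 | 0.99 | 0.64 | 1.43 |

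**3. Bias of the adjusted estimates that are reported.** The covariance of the adjusted and unadjusted estimates equals the variance of the adjusted one, (1 − R²)SE². So the mean adjusted estimate, given a significant unadjusted test, is d + (1 − R²) × SE × φ(c)/(1 − Φ(c)), with c = 1.645 − d/SE.
- d = 0.25: c = −0.045, ratio 0.770. R² = 0.10 gives 0.25 + 0.9 × 0.148 × 0.770 = 0.35; R² = 0.30 gives 0.33. As R² approaches 0 the limit is 0.36.
- d = 0.50: c = −1.734, ratio 0.0925, mean 0.51 for R² from 0.10 to 0.30.
- d = 0: c = 1.645, ratio 2.063, mean 0.27 (R² = 0.10) or 0.21 (R² = 0.30).

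A simulation with LA Year 5 numbers (117 and 73, three prognostic covariates fixed in advance, 6,000 runs per setting) agrees: 0.35 and 0.33 for a true 0.25, 0.51 for a true 0.50, and 0.28 and 0.21 for a true zero. Without the condition, the mean at a true 0.25 was 0.25.

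**4. Results forgone.** In the same simulation, the adjusted test would have been significant but was not run in 7.3% (R² = 0.10) to 16.4% (R² = 0.30) of trials at 0.25 SD, and in 2.1% to 4.0% at 0.50 SD. The type I error of the unadjusted test was 0.049 to 0.051.

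**5. Do the other planned models fill the gap?** Only in part. The growth-curve models carry demographic predictors without the condition, but those predictors are again assessed on the data. The section on developing the assessment plan places direct cognitive testing at 3 and 5 years only, so a growth curve has two occasions for the powered domain. The multi-measure, imputation and weighting models are not said to include baseline covariates.

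**The case against.** The best defence is that the conditional regression is a follow-up. The first-line test is an unadjusted intention-to-treat comparison, which is valid under randomisation, keeps its type I error and gives an unselected estimate for every primary outcome. An unadjusted primary analysis is a legitimate if less efficient choice, and at the design effect the loss is slight. Significant confounders may also mean important ones, and a covariate list may sit in a fuller plan that is not shown. All of this stands, and a missing list is not held against the article. What remains is the written condition itself, which a covariate list would not remove.

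Stronger readings are tempting but not supported:
- *Adjusted models run only after significance, and null outcomes never get one.* The same section plans growth-curve models with demographic predictors free of the condition, and nothing bars adjustment for null outcomes.
- *The article expects effects from below 0.25 to 0.50 SD.* It chose 0.50; the smaller figure describes earlier programmes from which it distinguishes its own.
- *The difference in child sex at LA in Table 2 (43.5% against 53.9% girls) shows the harm.* No whole number out of 165 or 120 gives those percentages (72/165 = 43.6%, 65/120 = 54.2%), so the denominators are unknown, and the difference does not bear on the condition. Nor does the reported baseline equivalence remove the case for adjustment, whose purpose here is precision.

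**Conclusion.** The point holds in limited form. The regression step depends on a significant unadjusted difference and its adjustment is for significant confounders, and it is the main adjusted analysis described for the powered outcome. At the design effect of 0.50 SD the cost is small: at most about 3 points of power and a bias of about 0.01 SD. At 0.25 SD it is material: about 4 to 13 points of power, and reported adjusted estimates about 0.08 to 0.11 SD too large. These sizes rest on the assumed R² of 0.10 to 0.30, the attained Year 5 numbers and a one-sided 0.05 first-step test. The unadjusted test itself is not in question. This should be changed, but it does not invalidate the trial's first-line comparison.

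**What to change.** For estimating the treatment effect, delete the condition that significant group differences must first be detected, and delete the word significant before confounders. For every primary outcome at each site, fit a regression or mixed model adjusted for one set of covariates fixed in advance, whatever the unadjusted result, and report the unadjusted estimate beside it.

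The covariates should be ones that allocation cannot change, because the article counts baseline assessments as a share of mothers already randomised (338 of 361 and 236 of 245). Maternal age, maternal education, home language, number of children in the home and child sex would serve as an example. The search for effect modification can stay as a separate, labelled follow-up.

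The cost is wording and analysis code; these variables already appear in Tables 1 and 2.
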